## Abstract

**Background:**

Colorectal cancer is one of the most common cancers and causes of cancer-related death. Up to approximately 70% of patients with metastatic colorectal cancer (mCRC) have metastases to the liver at initial diagnosis. Second-line systemic treatment in mCRC can prolong survival after development of disease progression during or after first-line treatment and in those who are intolerant to first-line treatment.

**Objective:**

The objective of this study is to evaluate the efficacy and safety of transarterial radioembolization (TARE) with TheraSphere yttrium-90 (^90^Y) glass microspheres combined with second-line therapy in patients with mCRC of the liver who had disease progression during or after first-line chemotherapy.

**Methods:**

EPOCH is an open-label, prospective, multicenter, randomized, phase 3 trial being conducted at up to 100 sites in the United States, Canada, Europe, and Asia. Eligible patients have mCRC of the liver and disease progression after first-line chemotherapy with either an oxaliplatin-based or irinotecan-based regimen and are eligible for second-line chemotherapy with the alternate regimen. Patients were randomized 1:1 to the TARE group (chemotherapy with TARE in place of the second chemotherapy infusion and subsequent resumption of chemotherapy) or the control group (chemotherapy alone). The addition of targeted agents is permitted. The primary end points are progression-free survival and hepatic progression-free survival. The study objective will be considered achieved if at least one primary end point is statistically significant. Secondary end points are overall survival, time to symptomatic progression defined as Eastern Cooperative Oncology Group Performance Status score of 2 or higher, objective response rate, disease control rate, quality-of-life assessment by the Functional Assessment of Cancer Therapy-Colorectal Cancer questionnaire, and adverse events. The study is an adaptive trial, comprising a group sequential design with 2 interim analyses with a planned maximum of 420 patients. The study is designed to detect a 2.5-month increase in median progression-free survival, from 6 months in the control group to 8.5 months in the TARE group (hazard ratio [HR] 0.71), and a 3.5-month increase in median hepatic progression-free survival time, from 6.5 months in the control group to 10 months in the TARE group (HR 0.65). On the basis of simulations, the power to detect the target difference in either progression-free survival or hepatic progression-free survival is >90%, and the power to detect the target difference in each end point alone is >80%.

**Results:**

Patient enrollment ended in October 2018. The first interim analysis in June 2018 resulted in continuation of the study without any changes.

**Conclusions:**

The EPOCH study may contribute toward the establishment of the role of combination therapy with TARE and oxaliplatin- or irinotecan-based chemotherapy in the second-line treatment of mCRC of the liver.

**Trial Registration:**

ClinicalTrials.gov NCT01483027; https://clinicaltrials.gov/ct2/show/NCT01483027 (Archived by WebCite at http://www.webcitation.org/734A6PAYW)

**International Registered Report Identifier (IRRID):**

RR1-10.2196/11545

## Introduction

Colorectal cancer is the third most common newly diagnosed cancer and the fourth most common cause of cancer death globally [1]. Metastatic disease is observed at first diagnosis in an estimated 25% of new patients (synchronous distant metastasis) [2] and eventually develops in a further estimated 60% of patients (metachronous metastasis) [2-4]. The prognosis for metastatic colorectal cancer (mCRC) remains poor, with a 5-year survival rate around 14% [5]; the 5-year relative survival is worse for patients with metachronous metastasis than for those with synchronous metastasis (17.6% vs 7.2%) [6]. The liver is the most common site of metastasis because the blood that drains from the bowel and colon goes through the portal vein, and the circulating tumor cells are deposited in the liver [7,8]. Up to approximately 70% of metastatic patients present with mCRC to the liver at the initial diagnosis [7].

Although the outcome for patients with mCRC has improved with the rapid progress in diagnostic techniques and treatments, for most patients with mCRC, treatment is palliative rather than curative because the majority of patients are not candidates for surgical resection [9]. In mCRC patients for whom cure is not possible, potential goals of treatment are to prolong progression-free intervals, prolong life, improve quality of life, palliate symptoms, shrink tumor size, and protect the normal liver parenchyma. Patients with mCRC to the liver can achieve a median overall survival of approximately 30 months [10,11].

Most patients with mCRC receive systemic chemotherapy with or without targeted biological agents. First- and second-line systemic therapies typically include a fluoropyrimidine combined with either irinotecan (FOLFIRI regimen) or oxaliplatin (FOLFOX regimen). Biologically targeted agents include vascular endothelial growth factor inhibitors and epidermal growth factor receptor inhibitors [12]. Liver-directed therapies, that is, transarterial chemoembolization (TACE) and transarterial radioembolization (TARE), are well established in the armamentarium for treatment of metastatic disease, mostly in the salvage setting. The delivery of chemotherapy or radioactive-labeled yttrium-90 (^90^Y) microspheres via the hepatic arteries is selective to liver tumors because liver tumors are mostly perfused via the hepatic arteries, whereas normal hepatic parenchyma receives blood from the portal venous system [13].

Most mCRC patients who receive standard first-line treatment with combination regimens and treatment with targeted biological agents eventually develop either intolerance, recurrence, or progression and require second-line treatment. TARE is a treatment option that could be considered for patients with unresectable colorectal cancer and liver-dominant metastases who are refractory to chemotherapy. In such patients, prospective and retrospective studies have demonstrated that TARE is feasible and may compare favorably with standard-of-care treatment [14-16]. A rationale for the combination of TARE and systemic therapy is that liver-directed treatment with TARE will better control liver disease and systemic therapy will control extrahepatic progression and micrometastatic disease.

Here, we report the design of the EPOCH study: A Phase 3 Randomized Clinical Trial Evaluating TheraSphere in Patients with Metastatic Colorectal Carcinoma of the Liver Who Have Failed First-line Chemotherapy (trial registration: clinicaltrials.gov NCT01483027). The EPOCH study is being conducted to evaluate progression-free survival and hepatic progression-free survival in patients with mCRC when TheraSphere is added to second-line standard-of-care chemotherapy. In the second-line mCRC treatment setting, the EPOCH study is expected to be the largest study of the comparison of locoregional therapy with TARE in combination with standard-of-care systemic therapy versus standard-of-care systemic therapy alone.

## Methods

### Overview of Design

The study is being conducted in accordance with the Declaration of Helsinki. Participating institutions obtained institutional review board approval of the protocol and informed consent form and are responsible for obtaining written informed consent from patients at screening (Multimedia Appendix 1).

EPOCH is an ongoing, open-label, prospective, multicenter, randomized, phase 3 clinical trial. The objective is to evaluate the efficacy and safety of TARE with TheraSphere in patients with mCRC of the liver who have disease progression on first-line chemotherapy with either an oxaliplatin-based regimen or an irinotecan-based regimen and who are eligible for second-line chemotherapy with the alternate regimen. All patients receive chemotherapy; however, in the TARE group, TheraSphere is administered in place of the second cycle of chemotherapy, with chemotherapy subsequently resuming. A maximum of 420 patients are planned to be randomized at up to 100 sites in the United States, Canada, Europe, and Asia. The 2 primary end points are progression-free survival and hepatic progression-free survival. The study objective will be considered achieved if at least one primary end point is statistically significant. All patients are to be followed prospectively from randomization to death until the predefined number of progression-free survival events, to allow the final analysis to be conducted, have occurred.

The study commenced enrollment with a single primary end point of progression-free survival, with hepatic progression-free survival as a secondary end point. Progression-free survival is a valid surrogate end point for overall survival for mCRC patients receiving first- and second-line systemic chemotherapy with or without the inclusion of systemic targeted therapies [17,18]. The expected benefit for patients receiving a liver-directed therapy is an increased duration of liver disease control. Accordingly, the efficacy of a liver-directed treatment can be evaluated and measured by hepatic progression-free survival. A survival benefit of liver-directed treatment could occur via improvement of hepatic progression-free survival. Other liver-directed therapies, such as intra-arterial chemotherapy infusion, radiofrequency ablation, or TACE with drug-eluting beads, have demonstrated improvement of overall survival through improved control of hepatic disease [19,20]; thus, the efficacy of a liver-directed treatment may be evaluated and measured by hepatic progression-free survival [21]. To demonstrate the clinical benefit of TARE in mCRC patients with liver metastases, hepatic progression-free survival was subsequently included as a second primary end point. Progression-free survival and hepatic progression-free survival will evaluate the 2 major determinants of progression (extrahepatic factors and intrahepatic factors).

Trained clinical research associates performed a site initiation visit with investigators and their teams before the start of patient screening. Patient medical records are reviewed in a timely manner to confirm eligibility and compliance with the study protocol. Data entries on the electronic case report forms are reviewed by the clinical research associate and compared with the medical records and study protocol on an ongoing basis. An independent data monitoring committee (IDMC) was established to oversee the conduct of the study. The IDMC met periodically to review enrollment, protocol deviations, and safety events. In addition, the IDMC conducted and reviewed an initial feasibility safety analysis and will evaluate the progression-free survival data at interim analyses for consideration of stopping the study early for efficacy. The IDMC was tasked to make formal recommendations to the study sponsor based on decision rules in the IDMC charter.

### Screening and Eligibility

Screening and baseline evaluations occur from day −14 to day 0, where day 0 is the day of randomization. Demographics, medical history, medications, prior treatment history, and Eastern Cooperative Oncology Group (ECOG) Performance Status score were documented. Patients undergo physical examination and have baseline clinical laboratory tests including blood chemistry, hematology, coagulation tests, and colorectal cancer tumor marker (serum carcinoembryonic antigen). Kirsten retrovirus-associated DNA sequence (KRAS) oncogene status is determined if it is not already known. Serum pregnancy tests were conducted for women of childbearing potential. Patients must have baseline images for disease evaluation (spiral computerized tomography [CT] or magnetic resonance imaging [MRI] of the abdomen, pelvis, and chest) taken within 28 days before day 0 (randomization) when first-line chemotherapy is completed or after, and images must show measurable target tumors in the liver according to Response Evaluation Criteria In Solid Tumors (RECIST) version 1.1 [22]. Tumor burden was estimated from CT scans (visual or volumetric assessment). Inclusion and exclusion criteria are shown in Textbox 1.

Eligible patients must discontinue first-line chemotherapy and biologic agents during screening for a washout period of at least 14 days. The intended second-line chemotherapy regimen, including any biological agents, and dosages are decided. Patients complete the Functional Assessment of Cancer Therapy-Colorectal Cancer (FACT-C) quality-of-life questionnaire during the screening period.

Inclusion and exclusion criteria for the EPOCH study.
**Inclusion criteria**
Age at least 18 years.Colorectal cancer with unresectable metastatic unilobar or bilobar liver disease and disease progression in the liver with either (1) oxaliplatin-based or (2) irinotecan-based first-line chemotherapy; patient must be eligible to receive second-line standard-of-care chemotherapy with the alternate regimen. The determination of unresectable was based on local consideration, provided that the treatment decision was made by a multidisciplinary team that included a surgeon.Primary tumor either resected or clinically stable.Baseline images with measurable target tumors in the liver according to Response Evaluation Criteria in Solid Tumors version 1.1 using standard imaging techniques taken within 28 days before randomization. Images must be taken at completion of first-line chemotherapy or after.Tumor replacement less than 50% of total liver volume.Eastern Cooperative Oncology Group Performance Status score of 0 to 1 from screening to first treatment on study.Laboratory parameters: serum creatinine up to 2.0 mg/dL, serum bilirubin up to 1.2× upper limit of normal, albumin at least 3.0 g/dL, and neutrophil count more than 1200/mm^3^ (1.2 × 10^9^/L).
**Exclusion criteria**
Prior external beam radiation treatment to the liver and prior intra-arterial liver-directed therapy (including transarterial chemoembolization or TheraSphere yttrium-90 microspheres therapy).Planned nonstudy liver-directed therapy or radiation therapy. Planned treatment with biological agents within 28 days before receiving TheraSphere.Confirmed extrahepatic metastases. Limited, indeterminate extrahepatic lesions in the lung and/or lymph nodes are permitted (up to 5 lesions in the lung, with each individual lesion smaller than 1 cm; any number of lymph nodes with each individual node smaller than 1.5 cm).History of hepatic encephalopathy; history of severe peripheral allergy or intolerance to contrast agents, narcotics, sedatives, or atropine that cannot be managed medically.Contraindications to angiography and selective visceral catheterization, such as bleeding diathesis or coagulopathy that is not correctable by usual therapy with hemostatic agents; contraindications to the planned second-line chemotherapy regimen.Pulmonary insufficiency or clinically evident chronic obstructive pulmonary disease.Cirrhosis or portal hypertension.Receipt of intervention for the Ampulla of Vater or compromise thereof.Clinically evident ascites aside from trace ascites on imaging.Unresolved toxicities related to cancer therapy that the investigator determines will continue and compromise patient safety.Significant life-threatening extrahepatic disease, for example, unresolved diarrhea or serious unresolved infections, such as human immunodeficiency virus, acute hepatitis B virus, or hepatitis C virus.

### Randomization and Stratification

Eligible patients are randomized on day 0 in a 1:1 ratio to either the control group or the TARE group. If the study is not stopped early for efficacy, approximately 210 patients will be randomized to each group. To randomize eligible patients, the study site contacts the central randomization office where randomization will be determined using assignment by a computer-generated randomization scheme. Upon randomization, each patient is assigned an identity code. To ensure that treatment groups are balanced, patients are stratified at randomization based on the extent of liver involvement (unilobar vs bilobar disease), type of first-line chemotherapy (oxaliplatin-based vs irinotecan-based), and KRAS status (wild type vs mutant). Additional factors permitting covariate analysis are captured at randomization but are not stratification criteria. These factors have been defined based on the planned covariate analyses. Patients randomized to either the control or the TARE group who are unable to receive their planned study treatment continue to be followed under their assigned study group for the purpose of the intent-to-treat analysis.

### Chemotherapy

The treatment schema is shown in Figure 1.

For both groups, second-line chemotherapy started within 21 days of randomization. If during the first-line chemotherapy, patients had received an oxaliplatin-based regimen, then during the EPOCH study, they receive a standard-of-care irinotecan-based chemotherapy. Those who received an irinotecan-based regimen as first-line therapy receive a standard-of-care oxaliplatin-based regimen in this study. Generally, second-line chemotherapy is given every 2 weeks for 6 to 12 cycles; chemotherapy is continued at the investigator’s discretion.

**Figure 1 figure1:**
[figure not shown]
Clinical trial schema for the TheraSphere microspheres EPOCH study. Eligible patients have a washout period of at least 14 days from previous chemotherapy and biologic agents. Second-line chemotherapy is started within 21 days of randomization. Control group: biologic agents are permitted starting at the first cycle of second-line chemotherapy. TARE group: biological agents are discontinued at least 28 days before TARE and are not permitted until the first cycle of second-line chemotherapy that occurs after TARE. HPFS: hepatic progression-free survival; PFS: progression-free survival; TARE: transarterial radioembolization with TheraSpheres™ microspheres.

Control group patients can receive biological agents starting with the first cycle of second-line chemotherapy. For the TARE group, one cycle of chemotherapy is administered before the TheraSphere treatment, and biological agents may only be added to the first cycle of chemotherapy regimen that occurs after the TheraSphere administration.

### Transarterial Radioembolization

In the TARE group, TheraSphere microspheres are administered in place of the second cycle of chemotherapy. The treatment approach for TheraSphere can be lobar or selective. Patients with unilobar disease receive TARE to the diseased lobe. Patients with bilobar disease receive treatment to both lobes via successive lobar infusions during the same treatment session. Biological agents must be discontinued for at least 28 days before TARE. Chemotherapy resumes 2 weeks after TARE, at which time treatment with biologic agents may be started.

Eligibility for TARE with TheraSphere microspheres is determined by evaluations that include a pretreatment angiography with technetium-99m macroaggregated albumin (^99m^Tc-MAA), followed by a^99m^Tc-MAA single-photon emission computed tomography (SPECT) or SPECT-CT scan to assess the potential for shunting microspheres to the lungs as well as the potential for the deposition of microspheres to the gastrointestinal tract. Repeat^99m^Tc-MAA may be needed for subsequent treatments to estimate cumulative lung shunt or to reassess gastrointestinal shunting. Patients are ineligible for TARE if radiation exposure to the lungs exceeds 30 Gy (or 50 Gy cumulative across all planned infusions, estimated during the dose calculation) or embolization cannot be performed to effectively block gastrointestinal blood flow from the hepatic arterial system. Randomized patients deemed ineligible for TARE continue with the planned second-line chemotherapy.

Radioembolization can be performed via a segmental or lobar approach, depending on operator preference and angiographic anatomy. The targeted administered dose is 120±10% Gy to the target volume, based on a single-compartment Medical Internal Radiation Dose model [23].

TheraSphere should be administered by appropriately trained or designated personnel from the departments of radiology, nuclear medicine, and/or interventional radiology. Before the activation of trial sites with the appropriate approvals to administer TheraSphere, the health care professionals directly involved in the planning and administration of TheraSphere are required to attend a center of excellence training in which expert speakers lecture on topics related to patient selection and TheraSphere dosimetry and administration. Investigational teams must then accomplish at least three (or five) patient treatment cases with TheraSphere. The minimum number of cases is determined by a trained team of study sponsor proctors who review the treatment planning and perform on-site review of treatment administration. Upon completion of the training program, investigators are trained on the study protocol.

### Treatment for Disease Progression

After disease progression is observed and confirmed, patients in either group may receive the best alternative therapy or care that the investigator considers appropriate. Patients in the TARE group who have hepatic progression with hepatic lesions that are still amenable to TheraSphere are eligible for repeat treatment with TheraSphere. In these patients, TheraSphere may be administered at the investigator’s discretion on separate treatment days. Although this is not a cross-over study, patients in the control group who have hepatic progression with hepatic lesions that are amenable to liver-directed therapy can receive TheraSphere or any other liver-directed therapies according to the investigator’s decision. As with the initial administration of TheraSphere, biological agents must be discontinued for at least 28 days before any additional TheraSphere administration.

### Follow-Up Evaluations

The schedule of postrandomization evaluations is shown in Table 1.

Efficacy assessment scans are taken according to standard-of-care clinical management guidelines every 8 weeks (±1 week) after randomization until either death, withdrawal from study follow-up, or end of the study. The imaging modality used at baseline must be used throughout the study. Image assessment must follow study imaging guidelines. Tumor response is evaluated locally according to RECIST version 1.1. In case of progression, a confirmatory scan is requested. If the first progression occurs outside the liver, efforts must be made to continue the scheduled follow-up until hepatic progression occurs; no confirmatory scan is requested. Imaging performed for disease assessment must be submitted to the sponsor or designate for centralized review. Adverse events, serious adverse events, and unanticipated adverse device effects, as defined by the study protocol, will be collected throughout the study.

Independent review of the CT and MRI images is performed by a central imaging review organization. Central image review interpretation (independent reads by 2 radiologists with adjudication, if required, by a third radiologist) is performed in a blinded fashion on the full set of patient images and captured on an electronic case report form. The results of the primary study end points will be based on the central image review findings.

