### Efficacy End Points and Definitions

The primary efficacy end points of the EPOCH study are progression-free survival and hepatic progression-free survival. The secondary efficacy end points are overall survival, time to symptomatic progression, objective response rate, disease control rate, quality of life assessment by FACT-C questionnaire, and adverse events. Definitions of these outcomes are as follows:

Progression-free survival is the time from the randomization date to the date of radiological progression or death from any cause, whichever occurs first. Radiological progression is determined by blinded central image review according to RECIST version 1.1.Hepatic progression-free survival is the time from randomization to the date of radiological progression in the liver or death from any cause, whichever occurs first. Radiological progression is determined by blinded central image review according to RECIST version 1.1.Overall survival is the time from the randomization date to death from any cause.Time to symptomatic progression is the time from randomization to ECOG Performance Status score greater than 2 points. Such deterioration in performance score is to be confirmed at one subsequent evaluation at least 8 weeks later.Objective response rate is the proportion of patients achieving a best tumor response of either complete response or partial response during the study, as assessed by blinded central image review according to RECIST version 1.1.Disease control rate is the proportion of patients achieving a best tumor response of either complete response, partial response, or stable disease during the study, as assessed by blinded central image review according to RECIST version 1.1.Quality-of-life assessment is based on the patient-reported FACT-C questionnaire. Deterioration in quality of life is a decline of at least seven points in the total FACT-C score or death, whichever occurs first. The time to deterioration in quality of life is calculated as the time from randomization to deterioration in quality of life.

TARE can cause tumor inflammation (edema) early after treatment; therefore, any tumor assessments performed within six weeks of randomization will not be included in the analysis of imaging-related efficacy end points to rule out the risk of false progression.

**Table 1 table1:** Schedule of events after randomization on day 0.

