Interventions and assessments		Chemotherapy	First TARE^a^ workup and administration in TARE group	Study visits to progression	Additional TARE workup and administration^b^	Study visits until death or end of study
Description		Every 2 weeks	Replaces second cycle of chemotherapy	Every 8 weeks from day 0 (±1 week)	After hepatic progression, TARE replaces a cycle of chemotherapy	Every 8 weeks (±1 week)

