**Assessments**						
	ECOG^f^ Performance Status	✓^g^	✓	✓	✓	✓^g^
	Hematology^h^, chemistry panel, liver function tests	✓	—	✓	✓	—
	Coagulation tests^i^	✓^j^	—	—	✓	—
	Serum pregnancy^k^	—	✓	—	✓	—
	Tumor markers for colorectal cancer (serum carcinoembryonic antigen)	—	—	✓	—	—
	Record and administer any chemotherapy following second-line chemotherapy^l^	—	—	—	—	✓
	Quality-of-life questionnaire	—	—	✓	—	✓^g^
	Spiral CT^m^ or MRI^n^ of the abdomen, pelvis, or chest^o^	—	—	✓	✓	—
	Assess and report adverse events	✓	✓	✓	✓	✓
	Review and record concurrent medication	✓	✓	✓	✓	✓
	Final end point, efficacy and safety documentation, and exit patient	—	—	—	—	✓

^a^TARE: transarterial radioembolization.

^b^In lesions amenable to further TARE.

^c^^99m^Tc-MAA: technetium-99m macroaggregated albumin.

^d^Before TARE administration.

^e^Assessment or intervention was not conducted at that time.

^f^ECOG: Eastern Cooperative Oncology Group.

^g^Can be done remotely if patient is not coming in for clinic visit.

^h^Hematology tests: white blood cells with differential, hemoglobin, hematocrit, and platelets.

^i^Coagulation tests: prothrombin time, partial thromboplastin time, and international normalized ratio.

^j^Only required at chemotherapy visits as clinically indicated, that is, if patient is being followed for coagulopathy.

^k^Required for female patients of childbearing potential.

^l^All randomized patients must receive chemotherapy within 21 days of randomization.

^m^CT: computed tomography.

^n^MRI: magnetic resonance imaging.

^o^All attempts should be made to obtain imaging every 8 weeks until hepatic progression, plus confirmatory scan.

The following additional efficacy variables will be assessed:

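### The text images until death or study end, but Table 1 and its footnote end imaging at progression without saying whose reading counts, so centrally read HPFS (and sometimes PFS) can go unobserved

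*Protocol article*

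**What the plan says.** The article gives the end of efficacy imaging in four places.

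- **Follow-Up Evaluations, opening rule:** scans are taken "every 8 weeks (±1 week) after randomization until either death, withdrawal from study follow-up, or end of the study".
- **Follow-Up Evaluations, later in the same paragraph:** "If the first progression occurs outside the liver, efforts must be made to continue the scheduled follow-up until hepatic progression occurs".
- **Table 1, columns:** the CT/MRI row is ticked under "Study visits to progression" and under additional TARE. It has a dash under "Study visits until death or end of study". The heading does not say which kind of progression, or read by whom.
- **Table 1, footnote o, attached to the imaging row:** "All attempts should be made to obtain imaging every 8 weeks until hepatic progression, plus confirmatory scan".

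The body regions differ as well. Screening and Eligibility asks for "magnetic resonance imaging [MRI] of the abdomen, pelvis, and chest" at baseline, while the follow-up row of Table 1 reads "Spiral CT^m^ or MRI^n^ of the abdomen, pelvis, or chest^o".

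Two further facts matter. Tumor response is evaluated locally in an open-label trial, but the primary results are to be based on blinded central review. And "Hepatic progression-free survival is the time from randomization to the date of radiological progression in the liver or death from any cause, whichever occurs first", so a patient whose first progression is outside the liver is still at risk for this end point.

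**The concern.** The opening rule of the text and the dash in the last column of Table 1 cannot both be followed. Sites often work from the schedule table, so the discrepancy can decide whether later scans exist.

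Two routes lead to a missing primary outcome.

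1. **Local progression that central review does not confirm.** Imaging may stop after the local call (under footnote o, after one confirmatory scan). Central HPFS is then unobserved unless the patient dies. So is central PFS if no other progression has been read centrally.
2. **Extrahepatic progression first.** A site that follows only the column heading stops imaging there, and HPFS is unobserved from that date unless the patient dies.

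Either primary end point alone can make the trial positive. Loss of follow-up that depends on disease course is therefore worth preventing, and no analysis rule recovers a scan that was never taken.

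**Working it through.** **Which reading observes what**

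| Source | Imaging ends at | HPFS after extrahepatic progression | HPFS after local-only liver progression |
|---|---|---|---|
| Text, opening rule | death, withdrawal, study end | observed | observed |
| Text, later sentence | hepatic progression (effort) | observed if the effort succeeds | not secured |
| Footnote o | hepatic progression plus confirmatory scan (effort) | observed if the effort succeeds | not secured |
| Bare column heading | progression, type unspecified | not observed | not observed |

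Only the opening rule covers both routes.

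**Inputs** (Sample Size Estimate and the final-analysis section): median PFS 6 vs 8.5 months; median HPFS 6.5 vs 10 months; 420 patients, 36 months of accrual plus 12 of follow-up, 10% lost; 344 PFS events; final critical values 2.312 and 2.562. Hazards are taken as constant, λ = ln 2 / median.

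**Step 1: reproduce the plan's event count.** Evaluable patients: 420 × 0.9 = 378, or 189 per arm. P(event) = 1 − (e^(−12λ) − e^(−48λ)) / (36λ).
- PFS: control 0.941, TARE 0.879; 189 × (0.941 + 0.879) ≈ 344. This matches the stated 344.
- HPFS: control 0.929, TARE 0.840; 189 × (0.929 + 0.840) ≈ 334. The article states no HPFS event count.

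**Step 2: share of PFS events that are extrahepatic first**, treating the whole PFS–HPFS gap as extrahepatic progression: (λ_PFS − λ_HPFS) / λ_PFS.
- Control: (0.1155 − 0.1066) / 0.1155 = 7.7%.
- TARE: (0.0815 − 0.0693) / 0.0815 = 15.0%.
- These imply extrahepatic hazards of 0.0089 and 0.0122 per month. If TARE instead had the control value with its HPFS median kept: 0.0089 / (0.0089 + 0.0693) = 11.4%.

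**Step 3: events lost if all imaging stopped at first progression.** Extrahepatic-first patients: control 189 × 0.941 × 0.077 ≈ 14; TARE 189 × 0.879 × 0.150 ≈ 25. HPFS events left: 344 − 39 = 305. Loss: 334 − 305 = 29, and 29 / 334 ≈ 9%. This also drops deaths after imaging stopped. Deaths are HPFS events by definition, so for this route the figure is on the high side.

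**Step 4: power for HPFS** (2,000 simulated trials cut at 344 PFS events, simulation error about 0.6 points, liver hazard unchanged after extrahepatic progression).
- At z = 2.312: 93.2% with full follow-up, 91.2% if censored.
- At z = 2.562: 89.7% and 86.6%.

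The closed form Φ(√(d/4) × |ln 0.65| − z) agrees in size: going from 335 to 300 events lowers power from 94.9% to 92.2% at one-sided .0104, and from 91.6% to 87.9% at .0052.

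**Step 5: hazard ratio.** In the same simulation the HPFS HR is 0.66 with and without the censoring if liver hazard does not change after extrahepatic progression. If it doubles or quadruples (an assumption; the article gives no figure), the HR is 0.68 or 0.69 with full follow-up and 0.66 or 0.65 when censored, a shift in favour of TARE.

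Locally called progressions that central review does not confirm are in none of these figures, because the article gives no discordance rate.

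**The case against.** The strongest defence is that the article already provides for HPFS. A footnote qualifies its row, so Table 1 read whole continues imaging to hepatic progression, and the later sentence of Follow-Up Evaluations says the same for a first progression outside the liver. On that reading the dispute is between two stop points that both reach liver progression. This largely stands: loss after extrahepatic progression needs a site to follow the bare column heading, or the effort to fail. It does not answer the local-versus-central question, which footnote o leaves open.

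A reader might infer more: that HPFS will be censored at extrahepatic progression, twice as often under TARE, giving informative and differential censoring of both primary end points. The article does not support this. It states no censoring rule, and such rules commonly sit in the SAP, which is not shown. The 7.7% and 15.0% shares depend on constant hazards and on the design alternative. With equal hazards in the two arms for both end points, the shares are equal too.

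The chest wording in Table 1 may be loose drafting, and the study imaging guidelines that sites must follow are not shown. It is a copy-edit, though a useful one, since patients may enter with small indeterminate lung lesions.

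**Conclusion.** The inconsistency is real and should be corrected; the end point does not fail because of it. The opening rule of the text conflicts with Table 1 and footnote o, and nowhere is it said whether a local or a central reading ends imaging.

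If all imaging stopped at first progression, the cost through extrahepatic progression would be about 9% of HPFS events and 2 to 3 points of power, which stays above the stated 80%. That rests on constant hazards and on attributing the whole PFS–HPFS gap to extrahepatic progression. More such patients in the TARE group is what the design medians imply (15.0%, or 11.4% with equal extrahepatic hazards, against 7.7%), not something the article states. Bias in the HR by this route needs the further assumption that liver risk changes after extrahepatic progression. The local-only route can affect PFS as well as HPFS, and its size cannot be derived from the article.

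**What to change.** Bring Table 1 and footnote o into line with the rule Follow-Up Evaluations already states:

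- Tick the imaging row in the last column of Table 1.
- Reword footnote o and the later sentence of the text so that 8-weekly imaging continues in both arms until death, withdrawal or study end, regardless of extrahepatic progression, locally assessed progression or new therapy.
- In the Table 1 imaging row, change *or* to *and* before chest, to match baseline.

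Stopping only at centrally confirmed hepatic progression is not advised: it would need real-time central reads returned to sites, which the article does not describe. The rule above needs none. The change concerns assessments only, not treatment.

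The cost is a clarifying amendment or site memo and some extra scans at sites now following Table 1, none beyond what the text already requires. Enrollment has closed, but the article describes the trial as ongoing, so the clarification can still protect the remaining follow-up.
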